# Data Analysis and statistical methods

Treatment-related primary outcomes included treatment coverage (i.e., percentage of seropositive patients up to 18 years of age at serodiagnosis that were treated with benznidazole relative to the number of seropositive patients in this age group who were eligible for treatment); treatment quality (based on individual completion, medication adherence – as determined by the average percentage of benznidazole pills taken relative to those provided for each specific time period- and ADR management --percentage of patients who presented ≥1 ADR and were able to complete treatment), and therapeutic response (detection of *T. cruzi* DNA by kPCR and qPCR in patients who completed the full treatment course and had ≥80% of medication adherence). Patients with three or fewer pill counts and those withdrawn from or who abandon treatment will be excluded from adherence estimates. The therapeutic response to treatment will be essentially measured by the proportion of patients who were qPCR-negative at 180 dpt among those who had been qPCR-positive before treatment.

Statistical analysis will include Friedman’s two-way non-parametric analysis of variance for testing differences among repeated measurements of biochemical variables before treatment and at 20 and 60 dpt; Kendall’s *K* as an index of concordance; Fisher’s exact test or χ^2^ tests for investigating two by two contingency tables of independent data, and exact McNemar significance probabilities for paired data with small cell frequencies. The nominal level of statistical significance is set at a *P* value of 0.05. All tests will be performed using Stata 12.

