## Treatment

Benznidazole (Radanil^®^, Roche) will be provided free of charge by the National Chagas disease program, and administered in two daily doses (5-8 mg/kg-day) during 60 days over April-July 2011 by parents or guardians in an outpatient setting. Tablets will be fractioned by an hospital pharmacist to match individualized dosing regimens. Benznidazole doses and a weekly calendar will be provided to each patient, parent or guardian for each 15-day period to keep record of the doses taken daily and facilitate monitoring of medication adherence.

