## Follow up

Monitoring of medication adherence and ADRs will be conducted by local healthcare agents in five weekly appointments at the health post or at the patient’s home where they will record the patient’s body weight and temperature, and the number of benznidazole pills remaining. The patients’ parents or guardians will notify the healthcare agents the onset of any adverse drug-related reaction, sign or symptom, or may directly communicate with the coordination team by cell phone. The research team will keep a treatment diary to record the doses administered, its timing, and any symptoms or problems related to treatment.

All ADRs detected during drug administration (i.e., type, date of onset and remission, duration, and specific treatment indicated) will be recorded in each patient’s clinical history. Patients showing a severe or moderate, prolonged exanthema combined with fever will be transported to the local hospital for medical evaluation. Temporary suspension or benznidazole dose reduction or treatment with corticoesteroids or antihistamines may be prescribed to patients with mild or moderate reactions. Healthcare agents will follow up the evolution of ambulatory patients until remission.

The local physicians will re-evaluate the patients’ clinical status at the healthcare posts or schools 10, 20-30 and 60 dpt, and add these results to each individual clinical history. Each clinical evaluation will include a semiologic exam and clinical laboratory tests at 20-30 and 60 dpt to assess the same variables as determined at baseline. A blood sample aliquot will be kept for serological and molecular diagnosis as described above. Additional blood samples will be collected at 180 dpt for serological and molecular diagnosis of *T. cruzi* infection. All sera collected at 0, 60 and 180 dpt will be tested in parallel to assess any decay in specific antibody titers relative to baseline values.

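### Adherence is scored against pills provided, so a long physician-ordered hold on dispensed pills can remove a compliant child from the primary therapeutic-response set

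*Protocol*

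**What the plan says.** Four statements in the protocol bear on this point.

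- **Adherence.** Data Analysis and statistical methods defines it, as part of the treatment-quality outcome, as the "average percentage of benznidazole pills taken relative to those provided for each specific time period". The only exclusions from adherence estimates are children with three or fewer pill counts and those who are withdrawn or abandon treatment.
- **Therapeutic response.** The same section lists this among the primary outcomes and assesses it "in patients who completed the full treatment course and had ≥80% of medication adherence". A later sentence gives the essential measure as the proportion qPCR-negative at 180 days among those qPCR-positive before treatment. That sentence does not repeat the completion and 80% conditions.
- **Supply.** Treatment runs "during 60 days over April-July 2011", and the section says: "Benznidazole doses and a weekly calendar will be provided to each patient, parent or guardian for each 15-day period".
- **Reactions and monitoring.** Follow up says: "Temporary suspension or benznidazole dose reduction or treatment with corticoesteroids or antihistamines may be prescribed to patients with mild or moderate reactions". It also says: "Monitoring of medication adherence and ADRs will be conducted by local healthcare agents in five weekly appointments". The research team keeps a diary of doses given, their timing and any problems.

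**The concern.** A pill handed out before a physician orders a hold stays in the denominator. If the family obeys and the pill is never taken, it does not enter the numerator. The ratio then records the physician's decision as the family's non-adherence, and none of the listed exclusions covers this case.

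Two primary outcomes are touched. Adherence, as a measure of treatment quality, is understated for such a child. The same ratio also decides who enters the therapeutic-response set, so entry depends in part on an adverse reaction that occurs after treatment has started. The section's measure of ADR management counts a child with a reaction who completes treatment as a success. The same child could be a success there and be dropped from the response result for low adherence.

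**Working it through.** The protocol states no expected adherence, suspension frequency or response rate, so there is no figure of its own to reproduce. The check applies its definition to an ordered hold.

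**Inputs from the protocol**
- Course: 60 days (Treatment).
- Supply: 15 days, so 60/15 = 4 supplies (Treatment).
- Pill counts: five weekly, so 5 × 7 = 35 days (Follow up).
- Threshold: at least 80% (Data Analysis and statistical methods).

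The protocol does not say whether its time period is the week between counts or the 15-day supply, so both are shown.

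**Assumptions**
- The held pills had already been provided and are not taken later.
- The hold falls within the counted days.
- The child takes every other dose, unless stated otherwise.

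**Hold of h days over the five weekly counts:** adherence = (35 − h)/35.
- h = 7: 28/35 = 80.0%, which passes.
- h = 8: 27/35 = 77.1%, which fails.

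**Hold of h days within one supply, averaged over four supplies:** adherence = [3 × 100% + 100% × (15 − h)/15]/4.
- h = 12: (300 + 20.0)/4 = 80.0%, which passes.
- h = 13: (300 + 13.3)/4 = 78.3%, which fails.
- h = 15: (300 + 0)/4 = 75.0%, which fails.

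**Child who also misses some doses.** With own adherence a over W days, the score is a(W − h)/W. It is below 80% when h > W(1 − 0.80/a). The values of a are assumed.
- a = 0.95: more than 5.5 days (W = 35) or 9.5 days (W = 60).
- a = 0.90: more than 3.9 days (W = 35) or 6.7 days (W = 60).

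**Dose reduction.** Take half the dispensed pills for 15 days, purely as an illustration, with the next supply already matched to the reduced dose. The unused amount is 7.5 days' worth.
- 60-day basis: (60 − 7.5)/60 = 87.5%, which passes.
- 35-day basis: (35 − 7.5)/35 = 78.6%, which fails.

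**Hold that starts in mid-supply, with the next supply deferred.** About half of one supply is unused: (50 + 100 + 100 + 100)/4 = 87.5%, which passes.

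**With pills prescribed as the denominator.** A child who follows every instruction scores (W − h)/(W − h) = 100% for any h below W. The order alone can no longer take the child below 80%.

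**The case against.** The case on the other side has four parts.

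- **Many managed reactions do not touch the ratio.** A reader might infer that the formula is wrong for every managed reaction. The protocol does not support that. Corticosteroids or antihistamines are listed as alternatives to suspension or reduction, and a reaction treated only with them leaves the pill count unchanged. This stands.
- **Supplies are short and individually prepared.** If the next supply is withheld or cut, the denominator shrinks too. If held doses are taken later, pills taken catch up with pills provided; the protocol does not say whether they are. On the supply basis, most of a single supply must go unused before a fully adherent child fails. This stands too. It makes dose reduction a weak route and limits the point to holds that are long enough, on pills already dispensed and not made up.
- **The 80% condition is a declared choice.** To ask how the drug performs with adequate intake, pills actually taken is the relevant quantity, whatever the reason for missing doses. This is a fair defence of a restricted analysis based on intake. It does not justify using the same ratio to describe how well families followed instructions. Nor does it settle which denominator the section intends, because the essential measure omits the condition.
- **The meaning of a full course may be left to a statistical analysis plan.** Agreed; the missing definition is not pressed here. The adherence formula, the threshold and the restricted set are fixed in the protocol itself.

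**Conclusion.** The point holds in a conditional form. As written, following a physician's order on dispensed pills that are not made up is scored as non-adherence. A hold of 8 or more of the 35 counted days, or of 13 to 15 days within one supply averaged over four, takes an otherwise fully adherent child below 80% and out of the primary therapeutic-response set. Shorter holds suffice for a child who also misses some doses.

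A reader might go further and infer that the clearance figure will be overstated by a known amount. The documents do not support this. The overstatement would be s × (p_kept − p_removed), where s is the share removed and the two p are clearance proportions, and the protocol gives none of these. With assumed values of p_kept = 95%, s = 5% to 20% and p_removed = 70% to 95%, the result runs from 0 to 0.20 × 25 = 5 points. That range illustrates the formula and is not an estimate. Optimistic selection is plausible, because the set is conditioned on tolerating and completing treatment, but its size is unknown.

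Separately, the section supports two response denominators: completers with at least 80% adherence, and all patients qPCR-positive before treatment. The change should be made: it is cheap and affects two primary outcomes.

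**What to change.** Amend Data Analysis and statistical methods; no clinical rule changes.

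1. For the treatment-quality outcome, compute adherence as pills taken divided by pills prescribed for the period, net of ordered holds and reductions. Use the treatment diary and pill counts already planned in Follow up, and log each order in the diary with its dates.
2. Make the main therapeutic-response result the proportion qPCR-negative at 180 days among all treated children who were qPCR-positive at baseline. State how many have no 180-day sample.
3. Keep completers with at least 80% intake as a secondary analysis, defined by doses actually taken and not by the order-adjusted adherence in item 1. Otherwise children with a much reduced intake would enter it as fully adherent.
4. Reword the two sentences on therapeutic response so that each names its denominator.

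The cost is some wording and a little more analysis. No new visits or assays are planned for. The main clearance figure may come out less favourable, but it would describe the programme as delivered.

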**OBJECTIVE**

To develop, implement and test a strategy based on strengthened primary healthcare attention and broad social participation with the goals of increasing access to diagnosis and treatment of human *T. cruzi* infection in sparsely populated rural sections of Pampa del Indio municipality.

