### Criteria for withdrawal from the study

- Severe adverse reaction potentially attributable to benznidazole or not.
- Any situation that may put the safety of the patient at risk, according to the judgment of attending physicians.

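### Therapeutic response is defined only in adherent completers, the later 180-day measure leaves the denominator unclear, and no all-treated response is named

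*Protocol*

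**What the plan says.** The Data Analysis section names three groups of outcomes. It begins with "Treatment-related primary outcomes included treatment coverage" and goes on to treatment quality (completion, adherence, management of adverse drug reactions) and therapeutic response. Therapeutic response is PCR detection of parasite DNA "in patients who completed the full treatment course and had ≥80% of medication adherence".

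Two other sentences in that section bear on the denominator:

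- On adherence: "Patients with three or fewer pill counts and those withdrawn from or who abandon treatment will be excluded from adherence estimates".
- On response, which is to be essentially measured by the "proportion of patients who were qPCR-negative at 180 dpt among those who had been qPCR-positive before treatment".

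The Treatment section gives benznidazole "during 60 days over April-July 2011". The Follow up section has healthcare agents count remaining pills at "five weekly appointments at the health post or at the patient’s home", and plans a further blood sample at 180 days after treatment initiation (dpt) without limiting it to completers. The section on withdrawal from the study lists "Severe adverse reaction potentially attributable to benznidazole or not". The Objective reads "To develop, implement and test a strategy based on strengthened primary healthcare attention and broad social participation", with the aim of widening access to diagnosis and treatment. The Background says that the effectiveness of such programmes has still to be documented.

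**The concern.** The study tests a way of delivering treatment in a remote rural area. A response rate confined to children who finished the course with at least 80% adherence answers another question: how often parasite DNA becomes undetectable when the drug is taken adequately. Whether a child enters that set depends on tolerance, family support and the programme's own follow-up, all of which come after baseline.

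The second response sentence could be read as counting every baseline qPCR-positive child. Two analysts could therefore report different values for the same primary outcome and each cite the protocol. If the restricted value is taken as what the programme achieves among treated children, it may be too high.

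**Working it through.** **1. Who is in the denominator.** The defining sentence requires completion and at least 80% adherence. The adherence sentence gives no estimate to children who are withdrawn, who abandon treatment or who have fewer than four pill counts. On the plain reading, a child with no adherence estimate cannot be shown to reach 80% and drops out. The 180-dpt sentence requires only a positive qPCR at baseline. It does not lift the restriction, and it names no all-treated set.

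**2. How the pill-count rule acts.** If counts are made only at the five scheduled appointments, a child seen at three of them (5 - 2 = 3) has too few counts and is left out, whatever the true adherence. Five weekly appointments span about 5 × 7 = 35 days, and 35/60 = 58% of the course. Missed follow-up thus shrinks the denominator instead of lowering the result. It can also remove children who took all their tablets, so the excluded group is not made up only of poorly treated children.

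**3. Size.** The protocol gives no expected response, completion or adherence rate, so there is no figure of its own to reproduce. Every input below is an assumption:

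- pA, response in the restricted set: 95%.
- e, share of treated baseline qPCR-positive children who are excluded: 5% to 30%.
- pE, response in the excluded children: 0% to 75%.

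All-treated response = (1 - e) × pA + e × pE. Gap = pA - all-treated response = e × (pA - pE).

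| e | All-treated, pE = 0% | All-treated, pE = 75% | Gap (percentage points) |
|---|---|---|---|
| 5% | 90.25% | 94.0% | 1.0 to 4.75 |
| 10% | 85.5% | 93.0% | 2.0 to 9.5 |
| 20% | 76.0% | 91.0% | 4.0 to 19.0 |
| 30% | 66.5% | 89.0% | 6.0 to 28.5 |

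For example, at e = 20% and pE = 75%: 0.80 × 0.95 + 0.20 × 0.75 = 0.76 + 0.15 = 0.91, a gap of 4.0 points. If pE = pA, the gap is zero at every e.

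**4. Withdrawal and the 180-dpt sample.** The withdrawal heading speaks of leaving the study, while the Follow up section plans the 180-dpt sample with no such limit. Read together, they leave open whether a child whose treatment is stopped after a severe reaction is still sampled. Without that sample, no later analysis can observe the child's response.

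**The case against.** The strongest reply is that response is only one of three groups of primary outcomes. The stated goal is access, which coverage measures. Children who stop or abandon treatment are not hidden: they lower completion, and those who stop because of a reaction also lower the adverse-reaction outcome. Clearance in children who took the drug is a coherent question, and the restriction is stated openly. No sample size, success threshold or group comparison depends on this set. All of this stands, and it limits the weight of the point.

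Five stronger readings are tempting, and the documents do not support them.

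- *That the restricted rate cannot be combined with the other outcomes.* It can: treated × (completed and adherent, given treated) × (cleared, given both) is a valid product. With 80% meeting both conditions it is 0.80 × 0.95 = 76%, the share treated, adherent and cleared. What is missing is the middle factor among baseline qPCR-positive children, since the protocol lists completion and average adherence but not their joint share.
- *That the plan has only a per-protocol response.* The 180-dpt sentence can be read otherwise. The sound criticism is that the two sentences are not reconciled.
- *That the excluded children are those most likely to fail.* Lower exposure makes this plausible, but the protocol has no data on it.
- *That the overstatement is known to be large.* The 28.5-point end needs 30% excluded and every one of them counted as a failure, which is an imputation and not an estimate of bias.
- *That withdrawn children will have no 180-dpt sample.* The wording leaves this open but does not say it.

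A separate analysis plan might add further analysis sets. The unclear denominator of a primary outcome would still need to be settled in the protocol, which is where it is fixed.

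**Conclusion.** The point holds in limited form. The protocol conditions one of its primary outcomes on completion and adherence, describes its denominator in two ways that do not match, and names no response among all treated children, although it sets out to test a delivery strategy. The restricted rate is a legitimate estimate of clearance under adequate exposure. It should not stand alone as the programme's response.

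Its distance from the all-treated rate cannot be derived from the documents. Under the assumptions shown it runs from about 1-5 points with 5% excluded to 6-28.5 points with 30% excluded, and it vanishes if excluded children clear equally often. The mismatch with the objective does not depend on those figures. This should be fixed, but it does not invalidate the coverage and treatment-quality outcomes.

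**What to change.** - Reconcile the two response sentences so that each reported rate has one named denominator.
- Report, as the programme-level response, the proportion qPCR-negative at 180 dpt among all baseline qPCR-positive children who received at least one dose, whatever their completion or adherence. Use observed results, and show missing counted as non-response as a sensitivity bound. Making that rule the main analysis is debatable, because it would mix loss to follow-up in remote villages with parasitological failure.
- Keep the rate in completers with at least 80% adherence beside it, labelled as the efficacy estimate, and give the share of treated baseline qPCR-positive children who meet both conditions.
- State in the withdrawal section that stopping the drug does not by itself end collection of the planned 180-dpt sample, where consent continues. This concerns data collection only and leaves the criteria for stopping treatment untouched.

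The cost is a few sentences in the analysis section and one in the withdrawal section. The 180-dpt sample is already planned. The downside is that the headline response may be lower.

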# study design

## Study type

Non-randomized prospective study in children residing in a well-defined rural endemic area.

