### Inclusion criteria

- Children of any gender or ethnic group, aged between 9 months and 18 years old, residents of Pampa del Indio Area I, seropositive for *T. cruzi* by at least two different techniques and eligible for treatment with benznidazole as per this treatment protocol.
  - Serodiagnostic criteria: At least 2 positive serological tests for *T. cruzi* infection using conventional (Chagatest, Wiener) and recombinant antigens (ELISA Rec V3.0, Wiener), and for serologically discordant sera indirect immunofluorescence antibody assay (Parasitest, Laboratorio IFI).
- Informed consent signed by the parent or guardian and consent of the patient. For community meetings including indigenous residents, explanations will be translated by an indigenous healthcare agent or by an appointed indigenous community member and consent will be obtained collectively and individually.

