## Patient recruitment

Patients found to be seropositive for *T. cruzi* and their parents or guardians will be summoned for a meeting conducted at the nearest rural school or healthcare post. Local physicians will communicate treatment benefits and eventual risks of ADRs to the patients. A locally adapted plan for monitoring ADR and medication adherence will be discussed and agreed upon.

Prior to the onset of treatment with benznidazole, the attending physicians will evaluate the patients’ clinical status at the healthcare posts or schools immediately before treatment (0 days posttreatment initiation, dpt) and record the results in an individual clinical history. Each clinical evaluation will include a semiologic exam, an electrocardiographic exam, and clinical laboratory tests to assess hematocrit and hemoglobin levels, platelets, white cell counts, alanine aminotransferase, aspartate aminotransferase and alkaline phosphatase, cholesterol, uremia, serum creatinine and serum proteins at the local hospital. Women in reproductive age will be tested for pregnancy. A blood sample aliquot will be kept for serological and molecular diagnosis as described above.

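### The main therapeutic-response measure is conditioned on one positive baseline qPCR with no untreated group, so intermittent detection counts as response; the full paired table should stand beside it

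*Protocol*

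**What the plan says.** Therapeutic response is one of three groups of primary outcomes in the Protocol's section Data Analysis and statistical methods, beside treatment coverage and treatment quality. That section describes it twice.

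- The wider description is "detection of *T. cruzi* DNA by kPCR and qPCR in patients who completed the full treatment course and had ≥80% of medication adherence". It does not require a positive baseline PCR, and it names no time point, contrast or rule for failure.
- The operational description begins "The therapeutic response to treatment will be essentially measured by" and continues with "the proportion of patients who were qPCR-negative at 180 dpt among those who had been qPCR-positive before treatment".

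The design is given under Study type as "Non-randomized prospective study in children residing in a well-defined rural endemic area", and no untreated or delayed-treatment group is described anywhere. Under Inclusion criteria, children must be "seropositive for *T. cruzi* by at least two different techniques and eligible for treatment with benznidazole as per this treatment protocol". A positive PCR is not required, so children who are qPCR-negative at baseline may be enrolled and treated.

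For the pre-treatment evaluation, Patient recruitment says "A blood sample aliquot will be kept for serological and molecular diagnosis as described above". Follow up plans further blood samples at 180 days for serology and PCR. Diagnostic surveys has each qPCR sample run in duplicate. The paired test listed is "exact McNemar significance probabilities for paired data with small cell frequencies", with no variable or population attached.

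**The concern.** Every enrolled child is infected by the study's own serological criterion. A negative qPCR in such a child before treatment therefore largely reflects what one blood sample can detect. If detection varies from one sample to the next, a group chosen because its first sample was positive will show fewer positives on the second, with or without treatment. This is regression to the mean applied to a yes/no assay. Without an untreated group, the conversion rate alone cannot show how much of itself is drug effect.

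The restriction also leaves out the children who would reveal the problem. A treated child who is negative at baseline and positive at 180 days is evidence of non-response, and such children show how much detection fluctuates. They enter neither the numerator nor the denominator of the main measure. Study area reports house infestation below 1% at the time of the serosurveys, with no infected bugs among those collected. Persistent infection with intermittent detection is therefore a more plausible explanation for such a result than reinfection.

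At stake is what the study may conclude about parasitological effect: the main figure can only be pushed in the favourable direction by this mechanism.

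**Working it through.** **Inputs from the Protocol.** No untreated group; entry by serology; one baseline aliquot and one 180-day sampling occasion; duplicate qPCR runs on the same sample, which address laboratory repeatability but not variation between bleeds. The Protocol states no sample size, expected response rate or qPCR detection rate, so there is no figure of its own to reproduce.

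**Assumed inputs.** s = mean probability that one sample from an infected, untreated child is qPCR-positive. r = within-child correlation of detection between two occasions. Neither is in the Protocol, so a range is shown.

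**Step 1: no drug effect, detection stable over time.**

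- P(positive at both) = s² + r·s(1 - s)
- P(positive at 180 | positive at 0) = s + r(1 - s)
- Apparent response = P(negative at 180 | positive at 0) = 1 - s - r(1 - s) = (1 - s)(1 - r)

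| s | r = 0 | r = 0.25 | r = 0.5 | r = 0.75 |
|---|---|---|---|---|
| 0.4 | 60% | 45% | 30% | 15% |
| 0.6 | 40% | 30% | 20% | 10% |
| 0.8 | 20% | 15% | 10% | 5% |
| 0.9 | 10% | 7.5% | 5% | 2.5% |

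A simulation of 1,000,000 children at s = 0.6 and r = 0.25 gave 0.299, against 0.300 from the formula.

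**Step 2: the full paired table under the same assumptions.** The two discordant cells are equal in expectation:

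P(+,-) = P(-,+) = s(1 - s)(1 - r)

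Take s = 0.6 and r = 0.5, per 100 treated children. The positive-to-negative cell is 100 × 0.6 × 0.4 × 0.5 = 12, and the negative-to-positive cell is also 12. Prevalence at 180 days is 60 - 12 + 12 = 60, so the net change is 0. The main measure would report 12/60 = 20% response from the same data.

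**Step 3: with a real drug effect.** Suppose a fraction c of baseline-positive children is cleared and stays negative, independently of how detectable each child was. The conversion rate is then c + (1 - c)(1 - s)(1 - r). The excess over c is (1 - c)(1 - s)(1 - r), which shrinks to 0 as c approaches 1. The distortion is therefore largest when the drug works least.

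**Step 4: limits of the net change.** If every child cleared, the conversion rate would be 100%, but at s = 0.6 the net fall in prevalence would be 60 percentage points. The two figures answer different questions.

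**The case against.** **Stronger readings that the Protocol does not support.** A reader might infer that response is scored in baseline-positive children alone and that negative-to-positive children are never counted. The wider description covers all adherent completers, and the word essentially makes the conditional proportion the main summary without excluding others. Such children could therefore be reported.

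A reader might also infer that McNemar's test will be run on the baseline-positive subset, where the negative-to-positive cell is empty by construction and six conversions would give an exact two-sided P of 2 × 0.5⁶ = 0.031. The Protocol does not tie the test to that subset, or to PCR at all. Applied to all paired results it would use both discordant cells, as it should.

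**Other evidence on response is planned.** There is a second PCR target (kPCR), aliquots are kept at the on-treatment evaluations, and antibody levels at 0, 60 and 180 days are compared side by side. These stand as supporting evidence, but they do not correct the qPCR conversion rate.

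**The denominator has a rationale.** A child negative at baseline cannot convert to negative, so using baseline positives to describe negativization is defensible. This stands, and is why the rate should be kept. It does not make the rate a measure of drug effect alone.

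**The size is not shown.** This also stands. With high, stable detection and a large true effect, the distortion would be small.

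**Importance.** The Objective is access to diagnosis and treatment, and no sample size or success threshold rests on the response figure. An analysis plan that is not shown might tabulate more. These points lower the priority. The denominator of the main measure is nevertheless fixed in the Protocol itself, and nothing there commits the study to the full table.

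**Conclusion.** The point holds for the main measure of therapeutic response. As written, that measure counts intermittent detection as response, always in the favourable direction, and leaves out children who go from negative to positive. With no drug effect its expected value is (1 - s)(1 - r): 2.5% to 60% over s = 0.4 to 0.9 and r = 0 to 0.75. Those inputs are assumptions, so the direction of the distortion is established but its size is not. The result also assumes that detection in an uncleared child does not change systematically between baseline and 180 days.

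The weakness limits what can be concluded about drug effect. It does not touch coverage, adherence or completion. It is a cheap improvement and not a must-fix.

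**What to change.** In Data Analysis and statistical methods, keep the conversion rate among baseline positives and add the following:

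- The full 0-by-180-day qPCR table for all treated children with both results, and again for the adherent completers the section already names.
- The net change in the proportion qPCR-positive, with its confidence interval, and the exact McNemar test applied to both discordant cells of that full table.
- A rule that any positive qPCR at 180 days counts as parasitological non-response, whatever the baseline result.
- A statement that the conversion rate is not to be read as drug effect alone.
- Where a child has qPCR results from both the diagnostic survey and the 0-day evaluation, the positive-to-negative rate between those two samples, as a pre-treatment reference. The Protocol does not make clear that such pairs will exist, so this item is conditional.

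The cost is wording: samples at 0 and 180 days are already planned for molecular diagnosis, so no extra visit is needed. The response figure may look less favourable. The net change is capped by baseline positivity, and without a control group it still assumes stable assay detection over time, so it should be reported beside the conversion rate and not in its place.
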